## Abstract

**Background:**

University is a period of increased vulnerability to mental health challenges, with anxiety and difficulties in emotion regulation among the most prevalent. Culturally adapted Cognitive Behavioral Therapy (CBT) and Dialectical Behavior Therapy (DBT) group interventions can support student well-being, yet scalable options remain limited. To address this gap, group CBT for anxiety management and group DBT for emotion regulation were culturally adapted for university students in Türkiye. Adaptations involved revising content and language, removing culturally mismatched elements, and incorporating culturally relevant and age-appropriate material.

**Purpose:**

This project aims to assess the feasibility and effectiveness of delivering culturally adapted group CBT for anxiety management and group DBT for emotion regulation.

**Methods:**

The project includes three steps: (i) a comprehensive systematic review of group CBT and DBT interventions worldwide; (ii) translation, adaptation, localization, and development of 8-session group interventions; and (iii) implementation, data collection, and analysis. Participants are allocated to either the CBT group for anxiety management or the DBT group for emotion regulation.

**Results:**

Standardized measures of anxiety or emotion regulation are administered at baseline, post-intervention, and six-week follow-up for both experimental and waitlist arms. Qualitative data are collected through semi-structured interviews conducted after intervention completion.

**Conclusions:**

In this project, the feasibility and effectiveness of culturally adapted CBT and DBT group interventions for university students in Türkiye will be evaluated. Findings will inform wider-scale application of evidence-based therapies in university counseling centres in Global South and guide the design of a future randomized controlled trial.

**Clinical Trials Information:**

NCT07096154 and NCT07096141 on clinicaltrials.gov.

Implications
**Practice:** University counseling centres can effectively address anxiety and emotion regulation challenges by integrating culturally adapted Cognitive Behavioral Therapy (CBT) and Dialectical behavior Therapy (DBT) group programs into their routine services.
**Policy:** Higher education and public health authorities should consider supporting the integration of culturally adapted evidence-based interventions into university mental health services to make them more relevant and accessible.
**Research:** More cultural adaptations of evidence-based therapies need to be investigated and trials across diverse universities should be conducted.

## Introduction

### Mental health of Turkish university students

University students’ psychological well-being is a prominent and growing public health issue worldwide [1]. The university period is a critical time for psychological, social and academic changes which may leave individuals more vulnerable to developing mental health problems [1]. It is suggested that almost one-third of students experience symptoms of common mental health disorders upon starting university [2]. In addition, students’ demand for university mental health support services has been increasing, which is above the rate of increase in the number of university students [3].

Research shows that university students in Türkiye are specifically at risk in terms of mental health in comparison to other countries. A systematic review covering countries such as China, Bangladesh, Spain, Russia, Korea, the US, and Japan reported a prevalence of 29% for anxiety, 37% for depression, and 23% for stress among university students, while in Türkiye, university students had much higher rates with 84.2% high stress, 36.2% high generalized anxiety symptoms, and 55% high depressive symptoms [4, 5]. Moderate and severe depressive symptoms of students in Türkiye have also been reported to be higher than the pooled international estimates [5]. Furthermore, national analyses conducted in Türkiye reveal that that 15–24 age group has the highest suicide rates which is consistent with WHO reports indicating that suicide is one of the top four causes of death among those aged 15–29 [6, 7].

### Access to mental health services in Türkiye

Despite the above-mentioned high rates of anxiety and emotion regulation difficulties, in Türkiye, accessible and free mental health services are usually restricted with 10-min psychiatric assessments, and psychological therapies are often a service people access paying out of pocket. In such circumstances, university mental health services become highly sought as some offer free or very low-cost psychological therapies. For this reason, evidence-based and cost-effective psychological therapies, such as group Cognitive Behavioral Therapy (CBT), and group Dialectical Behavior Therapy (DBT) informed interventions might constitute a solution.

### Group DBT informed and group CBT interventions

Research has shown that group based CBT and DBT can be effective intervention options that can promote mental well-being of university students [8, 9]. CBT has a significant evidence base established for treatment for anxiety disorders [10], and for this reason, recommended as first line of psychotherapy treatment by international health organizations such as National Institute for Health and Care Excellence [11, 12]. Research conducted internationally indicated the effectiveness of group CBT for anxiety management [13–15].

Group DBT interventions have been used and shown beneficial for emotion dysregulation related mental health difficulties [16]. Research has indicated that group DBT programmes can be effective for emotion regulation for university students and/or the 18–25 age group [17–23]. Furthermore, group CBT and DBT interventions provide a structure, foster companionship, limit the number of sessions, and can be cost and time effective for both the clients and the practitioners/services.

### Need for cultural adaptations for psychological therapies

It is accepted among mental health practitioners that an intervention that is customized for specific needs and contexts are more likely to be more helpful [24]. Furthermore, it is argued that Western conceptualisations of theories and interventions may not align with other cultures [25]. An example of this is that in many Western countries, therapist-client communication in therapy is on a first-name basis, whereas in Türkiye, clients often use more formal and hierarchical addresses such as “Ms/Mr/Dr” or “*Hocam*” (As an honorific title, *hoca* means “master” and is commonly used for teachers, professors, religious leaders, and in general, for wise people. It is also used as a slang word between friends.). This may indicate that participants in Türkiye may expect a more directive and mentorship-based intervention, at least at the beginning.

While following a very rigid fidelity to model approach in psychological interventions can provide structure and accountability, such rigidity also presents the risk of becoming an ineffective one-size-fits all method [24]. Various studies have suggested that culturally adapted interventions can promote positive mental health outcomes in different populations [26]. Cultural adaptation is not only about translation, it also necessitates localizing the structure and the delivery of the intervention tailored for the specific cultural context [27]. Psychological intervention methods developed in Western contexts may be less effective [24] not effective at all, and even harmful in different cultural contexts if values, norms and relationship dynamics are not considered.

However, despite seemingly desirable outcomes most of the group CBT and DBT interventions as explained above (see “Group DBT informed and group CBT interventions” section), these studies are predominantly conducted in the Global North, with minimal studies addressing adapting these therapy programmes for Turkish university students’ needs.

Although there are some studies investigating the effectiveness of CBT in reducing anxiety [28–32] and DBT in improving emotion regulation [33, 34] in Türkiye, feasibility studies in Turkish university students are scarce and little research has examined their practical implementation, engagement, and sustainability in real-world university settings, or analyzed clinical significance of the change. Furthermore, while some studies claim to have culturally adapted their interventions, they do not fully explain the localization process, making it difficult to assess the appropriateness and transferability of their methods [32–34]. Lastly, the unavailability of intervention manuals and protocols hinders replication and broader implementation.

To address this gap, it is essential for culturally adapted CBT and DBT group interventions to be created for Turkish university students and their effectiveness to be examined. We also hope that this study may serve as an example to other Global South countries with similar settings.

### Aims

This project aims to investigate the effectiveness of CBT based group anxiety and DBT-informed group emotion regulation interventions tailored for Turkish university students. The project also explores the feasibility of delivering these interventions in a group format within a university setting in Türkiye, and more specifically aims to: (i) test the feasibility and effectiveness of an adapted group CBT programme for anxiety management for Turkish university students; (ii) test the feasibility and effectiveness of an adapted group DBT-informed programme for emotion regulation for Turkish university students; (iii) investigate the thoughts, views, and experiences of Turkish university students who attended an adapted group CBT anxiety management intervention; (iv) investigate the thoughts, views, and experiences of Turkish university students who attended an adapted group DBT emotion regulation intervention.

Both interventions were systematically adapted to the cultural norms, lived experiences, and therapeutic needs of Turkish university students through a structured and progressive process. A detailed description of these adaptation procedures and concrete examples can be found in the Methods section (See “Second Stage—Cultural Adaptation of the Interventions” section).

## Method

### Project design

The project consists of three stages.

#### First stage—literature reviews

The first stage involves a comprehensive systematic review of group CBT and DBT interventions worldwide. Systematic reviews on the effectiveness of Cognitive Behavioral Therapy (CBT) based anxiety management groups and Dialectical Behavior Therapy (DBT) informed emotion regulation groups for university students were conducted to inform the intervention arm (third stage) of the study. Systematic review protocols are registered with Prospero with the registration numbers CRD42024590456 (CBT) and CRD42024575936 (DBT). Preliminary results indicate overall effectiveness for both interventions.

#### Second stage—cultural adaptation of the interventions

##### The team

Translation, adaptation, localization of an 8-session group CBT based anxiety management and DBT-informed emotion regulation interventions are led by a Turkish-speaking Clinical Psychologist and Assistant Professor (first author), and her team of Turkish trainee clinical psychologists, and trainee psychological counselors. Additionally, input was sought from a US trained and licensed Turkish Psychologist who has experience in university student mental health in the US and Türkiye.

The first author received her clinical psychology training in the UK, worked in the NHS with young people and young adults with anxiety and emotion regulation difficulties, and has supervisory experience in the UK and Türkiye. The team of trainee clinical psychologists and trainee psychological counselors are all educated and trained in Türkiye, thus, the entire team has direct familiarity with the cultural and educational context.

##### The framework

Barrero and Castro’s Heuristic Framework for its comprehensive, multidimensional and systematic structure was followed [35]. Consequently, the adaptation process consisted of the four stages: information gathering, preliminary adaptation design, preliminary adaptation tests and adaptation refinement. For the initial information gathering, comprehensive systematic reviews were conducted for group CBT and DBT interventions. Additionally, the needs and cultural context of the university population in Türkiye were assessed by the team through additional literature reviews, clinical observations, and expert opinions. Based on these findings, a preliminary adaptation design was created for both interventions by culturally adapting the language, examples, session content, and materials used in the intervention. As the cultural adaptation process do not end in this stage, further adjustments will be then made based on feedback obtained from participants and group facilitators during and after the feasibility trials, which is also recommended by Barrera Jr. & Castro [35]. The initial adaptation process for each group intervention is being further elaborated below.

##### Adaptation process for group CBT intervention for anxiety management

Group CBT for Anxiety Management is an 8-session intervention. Throughout the sessions, participants will be introduced to how CBT addresses anxiety and examine the connections between thoughts, emotions, physical responses, and behaviors. They will investigate the physiological effects of anxiety and practice relaxation techniques (e.g. breathing exercises, grounding techniques, progressive muscle relaxation). Participants will also learn to recognize their automatic thoughts and unhelpful thought patterns and will be equipped with effective strategies to challenge and reframe them. Additionally, they will strengthen their anxiety management skills through exposure to fear hierarchies and behavioral experiments. Finally, participants will be invited to decide the content of the seventh session to make it even more relatable to them.

The materials for CBT intervention has been selected by the first author using Beck’s and Padesky’s books [36, 37], choosing the components of CBT most relevant to the needs of our target population, rather than adapting the entirety of the resources. In this selection process, criteria such as feasibility of being able to be delivered in an 8-session group format, developmental characteristics of the population and suitability for the age group, and the applicability and the skill-focused structure of the content were considered. For example, techniques that require longer and more individualized therapeutic process or are difficult to implement in a group setting were not included. Examples that reflect the developmental characteristics of the population (e.g. identity formation, academic life, peer and romantic relationships, uncertainties about the future) were included in the content; examples that were developmentally less relevant to the university student population (e.g. parenting) were excluded so that the content would directly reflect and represent participants’ own experiences. These materials have been then translated into Turkish by the team of bilingual trainee clinical psychologists and trainee psychological counselors. The translated materials were then heavily edited and adapted to accommodate Turkish university students’ needs by the first author. Afterwards, the materials were checked by the rest of the team and changes were made based on the feedback the team provided.

The original framework of the intervention was retained, however, the first author created new examples that align with common experiences of university students in Türkiye such as bilingual education, academic worries, future and career related anxiety, relational and interpersonal problems, family conflicts and concerns related to developing autonomy from parents and family. Content and examples specific to this particular university, such as navigating university clubs, were also added. Additionally, CBT materials are prepared in a way that will allow group facilitators to bring their own examples. Considering that therapist self-disclosure often makes clients feel supported and validated, this format is intended to serve as a model for participants, encourage them to share their own experiences, reduce potential embarrassment or negative feelings that may arise in a group setting. The dynamic structure of the materials will facilitate better understanding and internalization of the content and provide data that will guide further refinement of the adaptation. For example, a facilitator might share how anxious they felt on a specific topic, and how they navigated this using CBT strategies. They will then encourage the participants to share their own examples. The impromptu examples brought by the facilitators then will be discussed in supervision to evaluate their suitability. Helpful examples that are consistent with the intervention framework may be incorporated into the ongoing adaptation of the protocol.

##### Adaptation process for group DBT intervention for emotion regulation

Culturally adapted group DBT-informed intervention for emotion regulation is designed to include 8 sessions, comprising the modules of mindfulness and emotion regulation [38]. Rather than adapting standard DBT for adults, session materials were derived from DBT for Adolescents, keeping in mind the age and this population’s dependency on their families. Mindfulness and emotion regulation modules of DBT [38] were selected by the first author because they are directly related to the focus of the intervention and are expected to be most effective in elevating the emotion regulation difficulties experienced by the university students. The criteria for this selection process included suitability for the 8-session group format, developmental characteristics, and age group appropriateness of the population, as well as the applicability of the content and its focus on skill building. These materials have been then translated into Turkish by the team of bilingual trainee clinical psychologists and trainee psychological counselors. The translated materials were then heavily edited and adapted to accommodate Turkish university students’ needs by the first author. Afterwards, the materials were checked by the rest of the team and changes were made based on the feedback the team provided. Furthermore, although the original manual includes parent-focused content, the first author heavily modified these sections, discarding any elements that could not be implemented within the group sessions.

Through the sessions, participants will work through the main problem areas that the DBT programme focuses on, familiarize with the three states of mind (emotion mind, reasonable mind, wise mind), practice mindfulness skills, get a better understanding of emotions and their functions, and work on improving emotion regulation skills through different exercises. To ensure cultural relevance, the content was systematically modified to include culturally relevant examples while maintaining the original framework of DBT. For example, Western political and popular culture references were replaced with Turkish ones. Furthermore, specific university-context elements were added including examples about campus-related situations, dormitory accommodation, interpersonal dynamics with faculty members, or dealing with academic workload. Everyday life examples were also modified by replacing culturally unfit elements with more relevant examples and scenarios to better reflect students’ and facilitators’ experiences (e.g. Turkish food instead of American food, using public transportation instead of driving, roommates/siblings instead of spouses). Additionally, to make the content more appropriate to the age group, elements related to video games, social media platforms (e.g. TikTok, Instagram) and online interpersonal behaviors (e.g. “ghosting,” “stalking,” “unfollowing”), which are highly relevant in lives of the young population today, were added. Also, based on the clinical anecdotes from the university counseling centre suggesting a significant number of neurodiverse students, selected sections were expanded to better reflect their experiences. Given the higher prevalence of sleep problems in this population, examples related to sleep were incorporated when addressing anxiety and emotion regulation. Additionally, relevant sections address sensory sensitivities in relation to emotional distress and anxiety. The material was also adapted to include other challenges neurodiverse individuals experience such as difficulty in planning, procrastination, sustained attention, time management, and social difficulty related anxiety and emotional regulation issues. Abbreviations, and acronyms were adapted to preserve both phonetic consistency and meaning in Turkish, ensuring that the content is engaging and impactful.

#### Third stage—implementation of culturally adapted interventions

The effectiveness and feasibility of both interventions will be investigated. This stage adopts a mixed-methods non-randomized pre-post design with a waitlist control and approximately 6 weeks follow-up. These feasibility studies are registered on clinicaltrials.gov with the identification numbers NCT07096154 and NCT07096141 for group CBT and group DBT interventions respectively.

### Participants

Up to 60 participants (experimental and control arms) for each study will be recruited from a university in Türkiye. We based our sample size on the study by Teare *et al.* [39], which recommended 60 participants per group for stable estimates of binary feasibility outcomes. We also aimed to maintain a minimum of 12 participants per group, as suggested by Julious [40], even in the worst-case scenario. Furthermore, it is a pragmatic decision considering the number of group facilitators needed to facilitate the groups and how many people we could include in each group.

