### Procedure

The language of the interventions, questionnaires, and the interviews are in Turkish. University’s psychological counseling centre is a stakeholder. An email invitation addressing the students and asking them to attend anxiety management or emotion regulation groups will be sent via the university’s psychological counseling centre. The volunteers who meet the clinical threshold for their respective groups will be invited to the groups on a first come first serve basis and receive either a group CBT intervention for anxiety-management or a group DBT-informed psychotherapy intervention for emotion regulation, based on their preference. If there are any volunteers who cannot be invited to the initial groups due to capacity, they will be placed on a waitlist and will be informed of this. All individuals who applied to join the groups will have eventual access to the intervention.

The interventions will last eight sessions and will be held on-site at campus in the university’s psychological counseling centre’s group rooms. The participants will not be allowed to attend the anxiety management and emotion regulation groups at the same time. The therapy groups will be facilitated by trainee or qualified clinical psychologists and/or trainee or qualified psychological counselors supervised by the first author. Data collection will be conducted online and in-session. For in-session quantitative data collection, separate research assistants will be employed. Further information on data-collection is provided below under “Data collection” section.

Participants will be asked to complete a batch of questionnaires at baseline, during and after the intervention, and after approximately 6 weeks follow-up. Furthermore, following the completion of the groups, qualitative data will be collected to explore the participants’ experiences and views on the group intervention they received. Although the study does not include an active control group, the waitlist controls will provide a reference condition that allows for comparison with the intervention group and enable a more accurate evaluation of the results. Tables 1 and 2 present full schedules of the assessment plans.

**Table 1 ibag010-T1:** Assessment Plan for the CBT group.

	Baseline assessment (t0)	Weekly assessment	Post-intervention assessment (t1)	Follow-up assessment (t2)
Socio-demographic Form	X			
Depression Anxiety and Stress Scale (DASS-42)	X		X	X
Beck Anxiety Inventory (BAI)	X		X	X

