## Data analysis

### Investigating the feasibility and acceptability of recruitment and delivery

To evaluate the acceptability and feasibility of these conducted groups, completion rates, number of attended sessions, drop-out rates, perceived burden and inconvenience of attending groups, and reasons for non-completion, the client feedback form and in-depth qualitative interviews will be investigated and/or analyzed.

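### The ceiling of 60 participants per study covers both arms, but it is justified by a recommendation of 60 per group, so the stated basis is not met

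*Protocol article*

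**What the plan says.** The protocol article gives the sample size in one short paragraph under Participants. The size is "Up to 60 participants (experimental and control arms) for each study will be recruited from a university in Türkiye". The parenthesis follows the number directly, so 60 is the total over both arms of one study. The next sentence takes the basis from a cited study, "which recommended 60 participants per group for stable estimates of binary feasibility outcomes".

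Two further grounds follow. One is a floor: "We also aimed to maintain a minimum of 12 participants per group". The other is practical: "it is a pragmatic decision considering the number of group facilitators needed to facilitate the groups", together with how many people each group can hold.

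The section on the third stage describes a "mixed-methods non-randomized pre-post design with a waitlist control and approximately 6 weeks follow-up", so each study has two arms. Under Procedure, places go to eligible volunteers in order of application, and the waitlist takes the overflow: "If there are any volunteers who cannot be invited to the initial groups due to capacity, they will be placed on a waitlist". The same section adds: "All individuals who applied to join the groups will have eventual access to the intervention".

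The feasibility measures under Data analysis include "completion rates, number of attended sessions, drop-out rates". The article gives no allocation ratio, expected proportion or precision target.

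**The concern.** A recommendation for each group has been used to support a total over two groups. The article presents the size as resting on a rule for stable binary estimates, and the planned number does not satisfy that rule as the article itself describes it.

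The binary measures most affected are completion and drop-out. They arise only among people who start a therapy group, so waitlisted students contribute nothing to them while they wait. These are feasibility studies meant to guide a later randomized trial, and completion and drop-out rates are among the figures that such a trial would take over. A reader who relies on the cited basis would credit those rates with the precision of 60 people per arm, when the arm that produces them will be smaller.

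**Working it through.** **Inputs from the protocol article**
- Ceiling per study, both arms together: 60 (Participants).
- Cited recommendation: 60 per group (Participants).
- Floor: 12 per group (Participants).
- Arms per study: 2, intervention and waitlist (third-stage section).
- Allocation: by capacity and order of application, no ratio (Procedure).

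**Assumptions, because the article gives no figure:** a true proportion of 50% or 80%, a two-sided 95% interval, independent participants, and enrolment that reaches the ceiling.

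**Step 1. Does the total follow from its basis?** 60 per group × 2 arms = 120 per study. The stated ceiling is 60, and 60/120 = 50%. The figure does not reproduce.

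**Step 2. How large can the intervention arm be?** With 60 enrolled and at least 12 in each arm, the most is 60 − 12 = 48 and the least is 12. An equal split gives 30. If fewer than 60 are recruited, the upper limit falls by the same number.

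**Step 3. What precision follows?** Half-width = 1.96 × √(p(1 − p)/n). For example, at p = 0.5 and n = 30: 1.96 × √(0.25/30) = 0.179.

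| n in the intervention arm | Half-width at p = 0.5 | Half-width at p = 0.8 | Width relative to n = 60, √(60/n) |
|---|---|---|---|
| 60 (cited basis) | 12.7 points | 10.1 points | 1.00 |
| 48 (largest, with 12 on the waitlist) | 14.1 points | 11.3 points | 1.12 |
| 30 (equal split, assumed) | 17.9 points | 14.3 points | 1.41 |
| 12 (stated floor) | 28.3 points | 22.6 points | 2.24 |

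**Step 4. Check with Wilson intervals at an observed completion near 80%.** 48/60 gives 68.2% to 88.2%; 38/48 (79%) gives 65.7% to 88.3%; 24/30 gives 62.7% to 90.5%; 10/12 (83%, since 80% of 12 is not a whole number) gives 55.2% to 95.3%. The pattern is the same as in the table.

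**The case against.** **The word group is used loosely.** The abstract and the table titles use it for the whole CBT or DBT programme. Read that way, 60 per group equals 60 per study and the mismatch disappears. This is the weaker reading. The parenthesis names both arms, and the floor of 12 per group in the same paragraph would then be the minimum for an entire two-arm study. It does suggest that a slip in wording is as likely as a design error.

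**The size has other support.** The floor of 12 is also a cited recommendation, and a total of up to 60 can satisfy it. The practical limit is a legitimate reason for a small feasibility study, and the Limitations section concedes a relatively small sample. All of this stands, so it would be wrong to say that the 60-per-group rule is the only statistical justification given. None of it makes a total of 60 agree with 60 per group.

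**The loss need not be half.** A reader might infer about 30 per arm at best. The article does not support that: with first-come allocation the intervention arm could reach 48, where the half-width at 50% is only 1.4 points wider than at 60.

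**The denominator could be larger.** Waitlisted students are promised the intervention, and the feasibility section does not restrict its measures to the first groups. Pooling their later delivery data is therefore not excluded, but it is not stated either. Questionnaire retention is measured in both arms and could use all 60 in any case.

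**Conclusion.** The point holds as a mismatch between the stated sample size and the basis given for it. A two-arm ceiling of 60 is half of the 120 that 60 per group implies. If the floor of 12 is kept in both arms, no split puts 60 people in the intervention arm.

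The cost in precision depends on a split that the article leaves open. At a true proportion of 50%, the half-width grows from 12.7 points to between 14.1 (n=48) and 28.3 (n=12), with 17.9 under an equal split. These figures assume full enrolment and independent participants. Members of one therapy group share facilitators and sessions, and any positive correlation between them would widen the intervals further. The check uses only the article's description of the cited recommendation, because the source itself was not available.

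A reader might also infer that the rates will be far less precise than the article promises. That goes too far: the article states no precision, and no decision rule in it depends on one. The appropriate grade is should-fix.

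**What to change.** 1. Correct the Participants paragraph. Say that 60 is the maximum over both arms of each study and that it does not meet the cited recommendation of 60 per group. Rest the size on facilitator and room capacity and on the minimum of 12 per group.
2. State the expected precision over the possible intervention-arm sizes, for example half-widths of 14.1, 17.9 and 28.3 points at n = 48, 30 and 12 for a proportion of 50%. Say that the allocation ratio is not fixed.
3. Record attendance, completion and drop-out when waitlisted students receive their group. Report these proportions with 95% confidence intervals for everyone who started a group, up to 60 per study, and show them separately by the arm in which each person was first placed.

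The third step goes beyond correcting the sentence, but it brings the denominator as near to the cited figure as the planned enrolment allows. The cost is a less favourable stated precision and attendance logs for sessions that are already promised. No extra participants are needed. Meeting the cited basis in each arm would instead take 120 per study, or 240 over both studies, which the practical limit appears to rule out.
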